#### Analysis

Participant characteristics will be described and summarised using standard statistics, and compared between sites and between time periods to verify that randomisation achieved reasonable comparability and identify any important changes in patient characteristics over time. Outcome analysis will be at patient level, clustered by ward. Outcomes will be presented as means or proportions and 95% confidence intervals. Analysis of geriatric syndromes will compare the difference in the proportion of participants developing any geriatric syndrome in the pre-intervention and post-intervention samples, under control and intervention conditions, to determine whether there is greater reduction on the intervention wards. Change in average length of stay will be compared using time to event analysis. Participants who are still in hospital at the end of the study period will be censored. Competing outcomes methods will be used to explore the impact of length of stay and discharge destination. Plots of the cumulative risks of discharge by length of stay will be compared between groups to examine the differences in detail and determine whether intervention effect varies by time in hospital. Modelling approaches (such as multiple logistic regression) will be used if needed to adjust for intergroup baseline differences. Planned subgroup analyses will be undertaken by site, by age (<75 versus 75 and older), and by frailty status. Cost-effectiveness will be assessed from the perspective of the healthcare system by modelling the change to total costs and total health benefits, with uncertainties included. The cost per quality adjusted life year gained from wider adoption of the program will be estimated.

We estimate a feasible recruitment of 250 participants for intervention and control ward in each period (i.e. 500 participants each in pre-intervention and post-intervention groups). This provides 80% power to demonstrate 30% reduction in geriatric syndromes in the intervention group, assuming 40% baseline prevalence, and a 15% reduction in acute length of stay assuming baseline of 9 days and SD 7 days. All analyses will be by intention to treat, i.e. all intervention group patients will be analysed as part of the intervention group even if they did not receive specific interventions.

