### Outcome evaluation

#### Participants and measures

Patients will be eligible to participate if they are aged 65 years or older, and admitted to any study ward during the study period, with an anticipated length of stay of three days or more. Exclusions are patients receiving end of life care, outliers from other teams, patients transferred or discharged from the ward within three days, and those with critical illness or severe cognitive impairment who cannot consent to participate and lack a surrogate able to consent on their behalf. Participants can only be enrolled once in the same study period, but the same participants could potentially be enrolled in both the pre-intervention and post-intervention samples during different hospital admissions.

Data will be collected by trained research assistants from patient (or surrogate) interview at four time points: admission (including assessment of health status prior to admission), day 5 of hospitalisation, discharge and 30 days after discharge from the treating team (the 30-day interview is by telephone). Data items for each interview are shown in Table 2. Additional data from structured review of the medical record will include demographics, diagnosis assigned by the treating team, co-morbidities, number of prescribed medications, previous hospitalisations, admission nursing assessments of common risk factors (vision, hearing, falls, pressure injuries, functional status, cognitive status, continence status), and consultations from allied health professional and other specialties. Baseline data from interview and medical record will be used to construct a frailty index based on the deficit accumulation model [35].

**Table 2 Tab2:** Interview data collection items and timing. Descriptions and references are included in main text

	Pre-admission	Admission (within72 h)	Day 5	Discharge (within 24 h)	Day 30
ADL	X	X	X	X	X
IADL	X				X
Malnutrition Screening Tool		X			
Depression (PHQ-2)	X				
Self-rated health	X				
Falls	X		X	X	X
Pressure injury		X	X	X	X
Bladder incontinence	X	X	X	X	X
Bowel incontinence	X	X	X	X	X
SPMSQ		X	X	X	X
3D-CAM		X	X	X	
EQ-5D				X	X

ADL activities of daily living: count of basic ADL (bathing, dressing, toileting, transferring, walking across and room, and feeding) requiring human assistance

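### The age subgroup analysis rests on one split at 75 although age is known in years; if the effect changes smoothly with age, roughly 25–47% of the information on that trend is lost

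*Protocol article*

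**What the plan says.** The Analysis section (Methods, Outcome evaluation) lists the subgroups in one sentence: "Planned subgroup analyses will be undertaken by site, by age (<75 versus 75 and older), and by frailty status". For age, both the cut and the number of groups are fixed. For frailty, only the word status is given, with no cut and no number of groups.

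Participants and measures shows what is available for each modifier. On age: "Patients will be eligible to participate if they are aged 65 years or older", with no upper limit. On frailty: "Baseline data from interview and medical record will be used to construct a frailty index based on the deficit accumulation model". The article gives no distribution for either variable.

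The primary comparison for the composite outcome is the pre-to-post change on intervention wards against the change on control wards. On numbers: "We estimate a feasible recruitment of 250 participants for intervention and control ward in each period". The power statement covers the two primary outcomes only; none is made for subgroups.

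**The concern.** A cut at 75 treats patients aged 75 and 95 as alike and patients aged 74 and 75 as different. Nothing in the article gives a reason to expect the effect to jump at that age. The Background describes geriatric syndromes as arising from baseline vulnerability, acute illness and the care environment together, which suggests a gradient more readily than a step. Under a gradient, a two-group indicator is a noisy stand-in for age, and the test of whether the effect varies loses power.

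At stake is how well the trial can say in whom the programme works. The article wants its results to inform wider adoption, so the question is relevant. The planned contrast is a change compared between arms, which is imprecise before any subgroup is formed, so there is little information to spare.

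**Working it through.** **1. The plan's own figure.** The article states: "This provides 80% power to demonstrate 30% reduction in geriatric syndromes in the intervention group, assuming 40% baseline prevalence". A 30% relative reduction from 40% gives 28%. With 250 against 250 and two-sided alpha 0.05 (assumed; none is stated), the usual two-proportion formula gives 81.0% power. The stated 80% is reproduced, but as a simple two-group comparison without clustering. The article gives no figure for subgroup power or information loss, so the rest rests on stated assumptions.

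**2. Precision of the planned contrast.** Take 250 per cell, 40% in three cells and 28% in the fourth, and ignore clustering.
- SE = √(3 × 0.40 × 0.60/250 + 0.28 × 0.72/250) = 0.0607
- 0.12/0.0607 = 1.976, so power = Φ(1.976 − 1.960) ≈ 51%

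This is the overall effect. A test of whether the effect varies starts from that base.

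**3. Information kept by the age split.** For a modifier that acts linearly, the share kept is the squared correlation between age and the indicator of age 75 or over:

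share kept = p(1 − p)(m₁ − m₀)² / Var(age)

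Here p is the proportion aged 75 or over, and m₁ and m₀ are the mean ages above and below the cut.

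For a uniform distribution starting at 65 this reduces to 3p(1 − p).

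| Assumed ages | p | Kept | Lost |
|---|---|---|---|
| Uniform 65–85 | 0.50 | 75% | 25% |
| Uniform 65–90 | 0.60 | 72% | 28% |
| Uniform 65–95 | 0.67 | 67% | 33% |
| Normal, mean 76, SD 8, limited to 65–100 | 0.60 | 62% | 38% |
| Normal, mean 78, SD 8, limited to 65–100 | 0.68 | 58% | 42% |
| Normal, mean 80, SD 8, limited to 65–100 | 0.76 | 53% | 47% |

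Worked example for mean 78: m₁ = 82.5, m₀ = 71.0 and the SD after truncation is 7.06. Then 0.681 × 0.319 × (11.55)² / 7.06² = 0.58.

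The plausible range is therefore a loss of about 25–47%. An older sample (normal, mean 82, SD 7) would lose 57%.

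**4. Frailty.** Using beta-distributed indices as an assumption, two groups lose 33–57%, three lose 17–19% and four lose 11–12%. The article does not say how many groups there will be, so no single figure applies.

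**5. What this means for power.** A logistic simulation with 250 independent patients per arm and period, clustering ignored and 600 runs gave these results for the arm × period × age interaction:

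| Interaction (log-odds per 8 years) | Age in years | Split at 75 |
|---|---|---|
| 0 | 4% | 5% |
| 0.6 | 50% | 33% |
| 0.9 | 80% | 53% |

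These gradients are steep. The whole planned effect, 40% to 28%, is a log-odds ratio of ln(0.28/0.72) − ln(0.40/0.60) = −0.54. The simulated gradients are thus 1.1 and 1.7 times that effect per SD of age.

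Rescale to half the planned effect per SD (0.27) by multiplying the non-centrality by 0.27/0.6 = 0.45:
- Age in years: 1.96 × 0.45 = 0.88, so Φ(0.88 − 1.96) ≈ 14%
- Split: 1.52 × 0.45 = 0.68, so Φ(0.68 − 1.96) ≈ 10%

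For a moderate gradient the gain is about 4 percentage points, and clustering would lower both figures.

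**The case against.** The strongest reply is that nothing here is an error. A pre-specified age cut is common practice, contradicts nothing in the article and cannot be picked after seeing the data. The subgroup analyses carry no power claim. This stands, and it limits the point to efficiency.

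It can also be said that the losses rest on assumed distributions and on linearity, and that a step at 75 would favour the split. This stands too, and is why a range is given with its condition. It does not remove the point: even the most favourable distribution tried loses a quarter of the information under a smooth gradient, and the article gives no reason for a step.

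The large power gaps in the simulation should not be used as a headline, because they need gradients larger than the whole planned effect per SD of age.

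Three stronger readings are tempting, and the article supports none of them:
- A reader might infer that the frailty index will be cut in two with a similar loss. The text says only "by age (<75 versus 75 and older), and by frailty status"; the form of the frailty grouping may well be set in a fuller document.
- A reader might infer separate tests within each subgroup in place of an interaction test. The article neither describes the former nor excludes the latter.
- A reader might take a single figure such as 40% as the loss for both modifiers. No distribution is given from which such a figure could be derived.

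**Conclusion.** The point holds for age, as a minor one. The article fixes a two-group age analysis where age in years is available. If the effect changes roughly linearly with age, the split loses about 25–47% of the information on that trend, assuming uniform ages from 65 or truncated normals with mean 76–80 and SD 8. If the effect steps at 75, it loses nothing.

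For frailty, the recommendation to use the continuous scale stands, without a fixed loss attached. In practice the gain is modest: about 14% against 10% power at half the planned effect per SD of age, before clustering. With 8 wards, any result on effect modification will be exploratory under either method.

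**What to change.** Reword the age part of the subgroup sentence so that effect modification is tested by a single arm × period × age interaction, with age in years, in the same ward-clustered model as the primary analysis. Check linearity with a simple spline. Report the estimated effect with its confidence interval at a few ages, for example 70, 80 and 90. Keep the groups under 75 and 75 or older for display. Treat the frailty index in the same way on its continuous scale, showing frailty groups descriptively, and label both analyses exploratory.

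The cost is one or two lines of analysis wording, with no new data and no planned output lost. The downside is the linearity assumption: if the effect really jumps at 75, the continuous test would be somewhat less efficient than the split, and a spline will have limited ability to show this in a sample of this size.

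### The stated 80% power for geriatric syndromes fits a two-group comparison; the planned pre/post-by-arm contrast has about 51% power before any allowance for ward clustering

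*Protocol article*

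**What the plan says.** All the relevant text is in the Analysis section of the protocol article (Methods, Outcome evaluation).

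- **Sample size:** "250 participants for intervention and control ward in each period (i.e. 500 participants each in pre-intervention and post-intervention groups"). This is 250 per arm per period and 1,000 participants in all.
- **Power:** "This provides 80% power to demonstrate 30% reduction in geriatric syndromes in the intervention group, assuming 40% baseline prevalence". No test, significance level, sidedness, intracluster correlation (ICC) or design effect accompanies the figure.
- **Planned comparison:** the analysis will "compare the difference in the proportion of participants developing any geriatric syndrome in the pre-intervention and post-intervention samples, under control and intervention conditions". Its stated purpose is to find out whether the fall is larger on the intervention wards. The Study design section describes the same comparison and gives control of hospital-wide change over time as a reason for it.
- **Clustering:** "Outcome analysis will be at patient level, clustered by ward". There are 8 wards, 4 per arm, with one ward per hospital randomised to each arm.

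**The concern.** The power sentence and the analysis sentence appear to describe different comparisons. A change-in-change contrast uses four estimated proportions instead of two. With equal cell sizes its variance is therefore about twice that of a two-group comparison. A sample just large enough for 80% power in two groups of 250 cannot also give 80% power for the four-cell contrast at the same effect.

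This is one of two primary outcomes. If the assumed 30% reduction is real, the planned analysis would miss it about half the time even under favourable assumptions. A reader who has been told that power was 80% could then give a null result more weight as evidence of no effect than it deserves.

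**Working it through.** **Inputs from the Analysis section.** 250 per arm per period; baseline 40%; relative reduction 30%, so 0.40 × 0.70 = 0.28, a difference of 0.12. **Assumed:** a two-sided 5% test, in keeping with the planned 95% confidence intervals; 40% in both pre-intervention cells and in the post-intervention control cell.

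**1. Reproducing the stated figure (two independent groups of 250).**
- Pooled proportion 0.34; SE under the null = √(2 × 0.34 × 0.66 / 250) = 0.0424.
- SE under the alternative = √((0.24 + 0.2016) / 250) = 0.0420.
- Power = Φ((0.12 − 1.96 × 0.0424) / 0.0420) = 81.0%.
- Variants: unpooled 81.5%, arcsine 81.1%, continuity-corrected 78.4%. For 80% power, 244 per group are needed (260 with continuity correction).

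The stated 80% is therefore reproduced.

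**2. The planned contrast, no clustering.** Cells 0.40 and 0.28 (intervention, pre and post) and 0.40 and 0.40 (control, pre and post).
- SE = √((3 × 0.24 + 0.2016) / 250) = 0.0607.
- Power = Φ(0.12 / 0.0607 − 1.96) = 50.7%. A simulation with 200,000 replicates gave 51.2%.
- Log-odds scale: effect 0.539, SE √((3/0.24 + 1/0.2016) / 250) = 0.264, power 53%.
- Log risk-ratio scale: effect 0.357, SE √((3 × 0.6/0.4 + 0.72/0.28) / 250) = 0.168, power 56%.
- Difference detectable with 80% power, holding the SE at 0.0607: 2.80 × 0.0607 = 0.170, or 17 points (0.17 / 0.40 = 43% relative).
- Cell size for 80% power at 12 points: 0.9216 × 2.80² / 0.12², about 503 per cell, hence about 2,012 participants instead of 1,000.

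**3. Clustering, for illustration only.** The article gives neither an ICC nor a correlation between a ward's effects in the two periods, so both are assumed here. With m = 250 / 4 = 62.5 patients per ward per period, the variance in step 2 is multiplied by f = (1 − ICC) + m × ICC × (1 − correlation). The t columns use a noncentral t distribution with 6 degrees of freedom (8 wards minus 2 arms). The detectable difference is about 3.37 × SE, where 3.37 is the noncentrality that gives 80% power.

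| ICC | Correlation | f | SE | Power, normal | Power, t on 6 df | Detectable at 80%, t on 6 df |
|---|---|---|---|---|---|---|
| 0 | – | 1.000 | 0.061 | 51% | 38% | 20 points |
| 0.01 | 0.8 | 1.115 | 0.064 | 47% | 35% | 22 points |
| 0.02 | 0.8 | 1.230 | 0.067 | 43% | 32% | 23 points |
| 0.05 | 0.8 | 1.575 | 0.076 | 35% | 26% | 26 points |

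With correlation 0.5, normal-reference power is 41%, 34% and 24% at ICC 0.01, 0.02 and 0.05. With correlation 1 (ward effects fully stable over time) they cancel from the contrast, and normal-reference power is 51% to 53% over the same ICC range.

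**The case against.** **The 80% is not a miscalculation.** For a plain two-group comparison it is correct, and the article names no test, so the two-group origin is an inference from arithmetic. That stands. The defect is a mismatch with the planned analysis, and it does not depend on where the 80% came from. A post-intervention comparison between arms, or pre versus post within the intervention wards, would fit the figure if patients were independent, but neither is the analysis described. Reading the plan as 500 per arm per period would give 79.8% for the four-cell contrast, but the article's own gloss of 500 participants in each period rules that out.

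**Clustering may not reduce power.** A reader might infer that power must fall below 51% once wards are taken into account. The document does not support that as a certainty. If ward effects are stable between periods and a normal critical value is used, power stays at 51% to 53%. The fall requires ward-by-period variation or a small-sample reference distribution.

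**The 6 df are a choice.** The article fixes no reference distribution. Since one ward per hospital goes to each arm, a paired ward-level test on 3 df is equally conceivable; with no ward variance it gives about 28% power. The ICC and small-sample method may properly sit in a fuller document that is not shown, so their absence is not the point here. The 51% uses neither.

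**The limits are partly acknowledged.** The Discussion concedes the small number of clusters, the sample is presented as what is feasible, and confidence intervals are planned. All true, but none of this qualifies the 80%. That a null result would actually be misread is a risk, not something the document shows.

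**Conclusion.** The point holds. The 80% power stated for geriatric syndromes does not apply to the analysis planned in the same section. For the pre/post-by-arm contrast with 250 per cell, power is about 51% on the risk-difference scale and 53% to 56% on ratio scales, before any clustering. Power of 80% is reached only for a reduction of about 17 points. These figures rest on a two-sided 5% test, 40% in the three unexposed cells and independent patients; they need no ICC.

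The further loss from clustering is conditional. With the assumed ICC of 0.01 to 0.05 and between-period correlation of 0.8, power is about 47% to 35% with a normal critical value and 35% to 26% with t on 6 df.

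The validity of the planned estimator is not in question, only the power claimed for it.

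**What to change.** Replace the 80% statement for geriatric syndromes with the power of the planned contrast:

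- Say that 250 per arm per period gives about 50% to 56% power, depending on the effect scale, for a reduction from 40% to 28% before allowance for clustering. State the significance level and sidedness.
- Add a range over stated assumptions for the ICC, the between-period ward correlation and the reference distribution.
- Give detectable differences computed under those same assumptions, without mixing them. For example: about 17 points unclustered with a normal reference; about 20 to 26 points with t on 6 df, for ICC 0 to 0.05 at correlation 0.8.
- State that a non-significant result will be interpreted from its confidence interval.

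This is a change of wording only. It needs no extra participants and leaves the design and analysis as they are. The cost is a stated power that looks less favourable.

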### Study design

We will use a cluster randomised control design, randomising one ward within each hospital (cluster) to implement the Eat Walk Engage program (intervention) and the other to continue usual care (control). Allocation will be undertaken by the off-site study statistician based on computer-generated random numbers using R [29].

Data will be collected on all 8 wards before and after an intervention period, with additional process data collected during implementation on intervention wards (Fig. 1). Outcome evaluation will compare measures in pre-intervention and post-intervention samples on the intervention wards, compared to measures in samples from the same time on control wards. This study design allows measurement of changes in processes and outcomes following intervention (to understand mechanisms of any observed outcome improvement) while controlling for systematic changes at hospital level which may affect the outcomes of interest. Patient-level data collection is planned for October 2015-March 2016 (pre-intervention) and October 2016-March 2017 (post-intervention).

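### The stated 80% power for a 15% shorter stay does not follow from its own inputs: 250 v 250 gives about 58% (two-sided 5%), and the planned change contrast less

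*Protocol article*

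**What the plan says.** All of this is in the protocol article, Methods, Outcome evaluation, Analysis, unless noted.

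- Size: "We estimate a feasible recruitment of 250 participants for intervention and control ward in each period", glossed as "i.e. 500 participants each in pre-intervention and post-intervention groups". That is 250 per arm per period, in four cells.
- Power for the first primary outcome: "This provides 80% power to demonstrate 30% reduction in geriatric syndromes in the intervention group, assuming 40% baseline prevalence".
- The same sentence continues, for the second primary outcome: "and a 15% reduction in acute length of stay assuming baseline of 9 days and SD 7 days".
- Planned analysis of that outcome: "Change in average length of stay will be compared using time to event analysis". Analysis is at patient level with clustering by ward.
- Planned contrast (Study design): the difference between pre- and post-intervention samples on intervention wards, set against the same difference on control wards.
- The power statement gives no alpha, sidedness, test or design effect. The nearest indication is "Outcomes will be presented as means or proportions and 95% confidence intervals".

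**The concern.** Length of stay is one of two primary outcomes, and the article prints the inputs and the resulting power together. A standardised effect of 1.35/7 = 0.193 is small for 250 per group, and 80% looks too high on sight. It looks higher still for a contrast between two changes, whose variance is twice that of a single-period difference.

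What is at stake is how the result will be read. If the stated power is taken at face value, a null finding on length of stay counts as fair evidence against a 15% reduction. If the real figure is well below 80%, it does not.

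**Working it through.** **Inputs from the article:** baseline mean 9 days, SD 7 days, reduction 15% (0.15 × 9 = 1.35 days), 250 per arm per period, geriatric syndromes 40% falling by 30% to 28%.

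**Assumed:** two-sided 5%, in line with the planned 95% intervals; independent patients; no design effect.

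**1. Find the convention from the other half of the sentence.** Two proportions, 250 v 250, pooled variance under the null:
- null SE = √(2 × 0.34 × 0.66 / 250) = 0.04237
- alternative SE = √((0.40 × 0.60 + 0.28 × 0.72) / 250) = 0.04203
- power = Φ((0.12 − 1.96 × 0.04237) / 0.04203) = Φ(0.879) = 81%

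The geriatric-syndrome figure therefore reproduces with 250 v 250, two-sided 5% and no clustering.

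**2. Length of stay under the same convention.**
- SE = 7 × √(2/250) = 0.626 days; 1.35 / 0.626 = 2.156
- power = Φ(2.156 − 1.960) = Φ(0.196) = 58%
- one-sided 5%: Φ(2.156 − 1.645) = Φ(0.511) = 70%
- n for 80% = 2 × (7/1.35)² × 7.849 = 422.1, so 423 per group
- detectable with 80% power at 250 per group: 2.802 × 0.626 = 1.75 days, and 1.75/9 = 19.5%

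**3. Planned change contrast, means scale, four cells of 250.**
- SE = 7 × √(4/250) = 0.885 days; 1.35 / 0.885 = 1.525
- power = Φ(1.525 − 1.960) = Φ(−0.435) = 33%
- detectable with 80% power: 2.802 × 0.885 = 2.48 days, and 2.48/9 = 28%

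**4. Sensitivity to an assumed log-normal stay.** Log SD = √ln(1 + (7/9)²) = 0.688; log ratio = −ln 0.85 = 0.1625.
- 250 v 250: SE = 0.688 × √(2/250) = 0.0615; power = Φ(2.642 − 1.960) = 75% two-sided, 84% one-sided
- change contrast: SE = 0.688 × √(4/250) = 0.0870; power = Φ(1.868 − 1.960) = 46% two-sided, 59% one-sided

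**5. Sensitivity to a time-to-event test.** Single period, 500 discharges, Schoenfeld: power = Φ(|ln HR| × √500 / 2 − 1.960).
- exponential stay, HR 0.85: 44%
- Weibull matched to mean 9 and SD 7, HR 0.81: 65%

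**6. Other groupings, means scale.**

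| Groups | Two-sided 5% | One-sided 5% |
|---|---|---|
| 250 v 500 | 70% | 80.1% |
| 250 v 750 | 75% | 84% |
| 500 v 500 | 86% | 92% |

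**7. Clustering, illustration only.** The article gives no intraclass correlation. Take 250/4 = 62.5 patients per ward per period and a design effect of 1 + 61.5 × ICC. Assumed ICCs of 0.01, 0.02 and 0.05 give 1.615, 2.23 and 4.075, and the 58% falls to about 40%, 30% and 19%.

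**The case against.** The best case for the plan is that alpha, sidedness and test are unstated, and that this is a condensed article whose fuller documents may name the method. A mean and SD can also parameterise a log-scale or rank-based calculation. So it is an inference, not a fact, that the authors compared means.

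Some readings do reach 80%. At 250 v 250, a one-sided test with an assumed log-normal stay gives 84% on the log scale and about 83% by simulated Mann-Whitney. One-sided 250 v 500 on means gives 80.1%, and 500 v 500 passes 80% two-sided. A reader might infer that no calculation with 250 per group can reach 80%, or that only 500 v 500 can. Neither is right.

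These readings do not rescue the printed figure. The article supports neither a one-sided test nor a log-normal distribution, and the pooled groups are not the contrast it describes. At 500 v 500 the syndrome figure would be 98%, so that grouping reproduces neither 80%. On the planned change contrast, even the one-sided log-normal reading gives only 59%.

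A reader might also take 33% as the power of the planned analysis. It is a means-scale approximation, and the plan specifies a time-to-event method whose power depends on the shape of the stay distribution. Nor does 58% by itself mean that the trial will probably miss the effect. Power below one half appears for the change contrast, under the exponential assumption or once clustering is allowed for.

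Finally, the sample was set by feasibility, and the Discussion concedes that there are few clusters. That explains the size but does not make the power figure correct.

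**Conclusion.** The point stands as an error in a stated figure. Under the convention that reproduces the paired outcome, the length-of-stay power is about 58% rather than 80%, a gap of about 22 points. This assumes two-sided 5%; one-sided 5% on the stated mean and SD still gives only about 70%.

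For the contrast the plan will actually test, power is lower: roughly 33% on the means scale to 46% if stay is log-normal, unclustered. That range is approximate, and the time-to-event figure may fall outside it. A ward design effect would reduce power further, by an amount the article does not allow one to fix.

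The 81% for geriatric syndromes serves here only to identify the convention. It is a single-period figure and says nothing about power for the planned change in syndromes. Nothing here calls the design, the endpoint or the analysis method into question.

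**What to change.** Remove length of stay from the 80% power claim. In its place give either the power for a 15% reduction or the reduction detectable with 80% power, calculated for the pre/post-by-arm change contrast under the time-to-event model. State alpha, sidedness, the test, the assumed distribution of stay and the allowance for ward clustering.

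Until that calculation is done, give approximate values and label them as such: about 58% for a single-period comparison of means, and roughly 33% to 46% for the change contrast, both before clustering. On the means scale the change contrast detects about 2.5 days (28%) with 80% power.

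The cost is wording and one calculation, and a less favourable printed figure. Recruitment, endpoints and conduct do not change.
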